**5-2-2. Obtaining consent for the fifth and subsequent doses of study drug in phase Ia part**

Prior to the fifth administration of the investigational drug, the investigator shall hand the subject an explanatory document containing the following information, explain it thoroughly, and obtain the subject's free and voluntary additional consent in writing for continued participation in this clinical trial. Other methods of obtaining consent shall be in accordance with "5-2-1. Obtaining Consent at the Start of the Clinical Trial".

1) The administration period to determine the maximum tolerated dose has been completed or is scheduled to be completed.

2) Purpose of the clinical trial

3) Name, title and contact information of the investigator(s)

4) Expected duration of subject's participation in the clinical trial

5) Participation in the clinical trial is of the subject's own free will, and the subject may refuse or withdraw from participation at any time. Further, refusal or withdrawal shall not cause the subject to be treated unfavorably or to lose any benefits to which he/she would be entitled if he/she did not participate in the clinical trial.

6) A consultation service at the site where subjects should inquire about or contact if they want further information about the clinical trial and their rights or if they experience any health problems related to the clinical trial.

7) Information that may influence the subject's decision to continue participation in the clinical trial should be promptly communicated to the subject.

8) Conditions or reasons for discontinuation of participation in the clinical trial.

**5-3. Notes on consent**

1) Before obtaining consent, the investigator should give the prospective subject an opportunity to ask questions and sufficient time to decide whether or not to participate in the clinical trial. At that time, the investigator or a collaborator acting as a supplementary informant shall answer all questions to the satisfaction of the prospective subject.

2) Neither the investigator nor the collaborator shall coerce or exert undue influence on the prospective subject with respect to participation or continued participation in the clinical trial.

3) In principle, the subject himself/herself should write, seal or sign the consent document. However, if the subject is unable to read the consent document and other explanatory documents, but is able to understand their contents orally or by other means of communication, an impartial witness is required at the time of explanation. The subject is given the consent document and other explanatory documents, the contents of which are explained orally or by other means of communication, the subject verbally agrees to participate in the trial, and the witness also signs and dates the consent form after the subject signs, seals, or stamps the consent form and dates it him/herself. The subject must also sign and date the consent form.

4) Explanations must not contain any words or phrases that would waive or imply waiver of the rights of prospective subjects, or that would waive or imply waiver of the legal responsibility of the investigator, sub investigator, collaborator, site, or person conducting the clinical trial. The information must not contain any words or phrases that would exempt or imply exemption from the legal responsibility of the investigators, sub investigators, collaborators, medical institutions, or those conducting the clinical trial themselves. 4) The language should be as non-technical as possible and understandable by the person who is to be the subject (including an impartial witness in cases where the person who is to be the subject is unable to read the explanatory document but is able to understand its content by oral or other means of communication).

5) The investigators plan to conduct genomic/genetic analysis for the evaluation of the investigational drug in this study, and will obtain written consent for the use of the provided samples for the purpose of genomic/genetic analysis after providing sufficient explanation to the prospective subjects in advance. The use of samples for genomic/genetic analysis may be conducted only with subjects who have given their written consent to the use of the samples. The investigator or sub investigator must explain to the prospective subject that the provision of the sample is based on the free will of the prospective subject, and that participation in this clinical trial is not dependent on the provision of the sample. If a subject wishes to withdraw consent after obtaining consent for the use of samples for the purpose of genomic/genetic analysis, a separate written consent withdrawal form must be submitted. If the investigational review committee of the investigational site does not approve the use of the sample, the sample will not be used for the purpose of genomic/genetic analysis.

**5-4. Revising consent and other explanatory documents**

1) When information is obtained that may influence the subject's intention to continue participation in the clinical trial, the investigator shall promptly inform the subject of such information and confirm the subject's intention to continue participation in the clinical trial. The date the information was given to the subject, the content of the information given, and the results of the confirmation shall be recorded in the original medical record such as the medical record.

2) When the investigator finds it necessary to revise the consent document and other explanatory documents (when new important information that may be relevant to the subject's consent is obtained), the investigator shall promptly revise the consent document and other explanatory documents based on such information and obtain approval from the investigational review committee in advance. In addition, the investigators shall promptly explain the revised consent document and other explanatory documents to subjects who are already participating in the clinical trial, and obtain their free will consent in writing for their continued participation in the clinical trial. However, consent is not required for subjects for whom administration of the investigational drug or observation has already been completed at the time of the revision. This does not apply to information regarding the progress of the clinical trial, such as fluctuations in general laboratory test values for individual subjects participating in the clinical trial.

**6. Investigational medicines**

All investigational drugs used in this clinical trial are manufactured, handled, stored, and controlled in compliance with the investigational drug GMP ("Standards for Manufacturing Control and Quality Control of Investigational Drugs (Investigational Drug GMP)" No. 0709002 dated July 9, 2008).

**6-1. Names**

Identification number: KW-0761

Generic name: Mogamulizumab (genetical recombination)

**6-2. Dosage form and ingredients**

The pH is adjusted to 5.0-6.0 by hydrochloric acid or sodium hydroxide. The concentration of mogamulizumab is 4.0 mg/mL, and 5 mL is dispensed in one vial.

**6-3. Molecular formula and molecular weight**

Molecular formula: C6520H10072N1736O2020S42

Molecular weight: approximately 146,443

Chemical structural formula: Glycoprotein consisting of two light chain molecules with 219 amino acids and two heavy chain molecules with 449 amino acids

**6-4. Storage methods**

Stored at 2-8℃ in a light-shielded container

**6-5. Validity period**

3 years from the date of manufacture

**6-6. Preparation of investigational medicinal products**

1) Do not shake the vial. 1) Do not shake the vial and do not agitate it vigorously.

2) When administering the drug, the required amount should be drawn off with a syringe and added to 200mL or 250mL of Japanese Pharmacopoeia saline solution.

3) Only Japanese Pharmacopoeia saline solution should be used for preparation.

4) After addition, mix gently and avoid rapid shaking.

5) Prepare the solution as needed and use it immediately after preparation. Discard any remaining liquid.

6) Do not mix with other drugs. 6-7.

**6-7. Packaging and labelling of investigational medicinal products**

1) Drug packaging

One box should contain 4 vials to make one unit. The box should be sealed by the investigational drug supplier.

2) Labeling

Labeling and packaging shall be described in the "Procedures for Administration of Investigational New Drugs," which will be separately stipulated.

**6-8. Provision of investigational medicines**

Investigational drugs are provided to each site in units of one box.

The investigator who conducts the clinical trial on his/her own shall not receive the investigational drug until the notification of the clinical trial plan to the Minister of Health, Labor and Welfare is accepted.

**6-9. Management of investigational medicines and return of unused investigational medicines**

(1) Storage and management of investigational new drug

The investigational new drug is provided by the investigational new drug provider to the investigator at each site at a predetermined time after the submission of the clinical trial plan. The investigator who conducts the clinical trial himself/herself explains the details of the clinical trial to the investigational drug manager at his/her site and submits the "Protocol for Management of Investigational Drugs" separately stipulated, and then requests storage and management of the investigational drug. The investigational drug manager shall appropriately store and manage the investigational drug, used vials, and outer packaging regardless of whether the investigational drug is used or not during the clinical trial period, and shall prepare an investigational drug management chart to monitor the usage status of the investigational drug. (2) The investigator who conducts the clinical trial shall check the consistency of the contents of the investigational drug control record, remaining drugs and case report forms, and if any inconsistency is found, immediately investigate the cause and make the necessary corrections.

(2) Return of unused investigational new drugs

After the completion of a clinical trial, the investigational drug manager shall return unused investigational drugs, empty boxes, and used vials to the person who conducts the clinical trial. When returning them, the subject's name (initials), medical record ID, and other information pertaining to the subject's privacy should not be legible. If unused investigational new drug, empty boxes or used vials are lost or disposed of, a record should be made of the details and reasons. (3) The sponsor shall submit all unused investigational new drugs, empty boxes and used vials returned by the investigational new drug manager to the secretariat of the TPC. The secretariat of the TIC shall properly dispose of all unused investigational new drugs, empty boxes, and used vials submitted by the investigator.

**7. Clinical trial methods**

**7-1. Clinical trial design**

[Phase Ia] Three patients (maximum 6 patients) in the Mogamulizumab 0.1 mg/kg group, followed by three patients (maximum 6 patients) in the 0.5 mg/kg group if the 0.1 mg/kg group is found to be well tolerated, and three patients (maximum 6 patients) in the 1.0 mg/kg group if the 0.5 mg/kg group is found to be well tolerated, at the prescribed dose. The investigational drug will be administered intravenously once a week for 8 consecutive weeks.

<Rationale for Dosing>

ATL, the current indication for which mogamulizumab is indicated, has various degrees of immunocompromised immunity, whereas patients with solid tumors usually have preserved immunocompetence. Therefore, the immune response induced in patients with solid tumors when regulatory T cells are removed by administration of mogamulizumab is stronger than that in ATL, and an autoimmune response is expected to occur simultaneously with an immune response to the tumor.

Furthermore, while Mogamulizumab administered to patients with ATL would be consumed primarily in response to CCR4-expressing tumors in the blood, Mogamulizumab in patients with solid tumors would be used primarily to remove a small number of regulatory T cells, resulting in a lower concentration of Mogamulizumab in the blood compared to patients with ATL. However, it is likely that in patients with solid tumors, mogamulizumab is primarily used to eliminate a small number of regulatory T cells, and blood levels may be higher than in patients with ATL.

In addition, a Phase I study conducted in patients with ATL showed that the 0.01 mg/kg dose of mogamulizumab was effective in eliminating regulatory T cells, and a 10-fold higher dose (0.1 mg/kg) of mogamulizumab would be effective in eliminating regulatory T cells in this subject population.

For these reasons, the risk of developing autoimmune diseases due to the regulatory T-cell elimination effect may be higher in patients with solid tumors, and therefore, the initial dose for patients with solid tumors should be set at 0.1 mg/kg, which is 1/10 of 1.0 mg/kg, the dose used for patients with ATL, to confirm the tolerability of the dose escalation. The initial dose was set at 0.1 mg/kg, 1/10 of the 1.0 mg/kg dose used in the study.

[Phase Ib] The patient population will be divided into 20 patients in each group, each of whom will receive one dose and 0.1 mg/kg, the highest dose among the doses that were found to be well tolerated in Phase Ia (one step below the MTD or 1.0 mg/kg if the MTD has not been reached). The dose should be administered intravenously once a week for 8 consecutive weeks. However, if the dose of 0.1 mg/kg was the only dose that was found to be tolerated in Phase Ia, a dose of 0.1 mg/kg will be used in Phase Ib for 20 patients in each group.

<Rationale for Dose Setting>

If the safety and regulatory T-cell effects of Mogamulizumab in solid tumors are confirmed by this study, it is assumed that a drug that releases immunosuppression by a mechanism different from that of Mogamulizumab may be used in combination with Mogamulizumab in the future. In such a case, the possibility of autoimmune reactions would be higher than with single-agent administration of Mogamulizumab. Therefore, the low dose group was set at 0.1 mg/kg, the lowest dose established in Phase Ia, in order to obtain data over a wide dose range for confirming regulatory T-cell removal efficacy. The low-dose group was set at 0.1 mg/kg.

In the Phase Ib study, the high-dose group and the 0.1 mg/kg group were used in the Phase Ib study.

For subjects who showed SD or higher in the regulatory T-cell test, antigen-specific antibody immunoreactivity test, or diagnostic imaging after 8 doses, if the subject wished to receive maintenance dosing of the study drug and if the investigators determined that maintenance dosing of the study drug was appropriate, the investigator or other appropriate personnel would administer the study drug to the subject. If the subject wishes to receive maintenance dosing of the investigational drug and the investigator determines that maintenance dosing is appropriate, maintenance dosing of the investigational drug is allowed every 4 weeks after 12 weeks until the discontinuation criteria are met.

[figure not shown]
Phase Ia: Starting at 0.1 mg/kg, dose escalation to 0.5 mg/kg and 1.0 mg/kg if tolerability is confirmed.

Phase Ib: Among the treatment groups that were found to be well tolerated, a high-dose group and two 0.1 mg/kg groups (if 0.5 mg/kg was the MTD in Phase Ia, one 0.1 mg/kg group) were administered. Enrollment to be 20 patients in each group.

**7-2. Group-to-group transition and procedures in phase Ia part**

The following procedure will be used to transition from the 0.1 mg/kg dose group to the 0.5 mg/kg dose group and then to the 1.0 mg/kg dose group. The Clinical Trial Coordinating Committee will decide on the transition of dosing groups. However, the efficacy and safety evaluation committee will also evaluate if necessary.

(1) If no DLT occurs in any of the 3 patients in the 0.1 mg/kg dose group, the patient will be shifted to the 0.5 mg/kg dose group.

If one of the three patients in the 0.1 mg/kg group develops DLT, three more patients will be enrolled in the 0.1 mg/kg group; if three or more patients in the 0.1 mg/kg group develop DLT, the MTD will be 0.1 mg/kg and the study will be terminated. If DLT occurs in 2 or less cases, the patient will be shifted to the 0.5 mg/kg group.

(2) If no DLT occurs in any of the 3 patients in the 0.5 mg/kg group, the patient will be moved to the 1.0 mg/kg group.

If 1 of 3 patients in the 0.5 mg/kg group develops DLT, enroll 3 more patients in the 0.5 mg/kg group. If more than 3 patients in the 0.5 mg/kg group develop DLT, the MTD will be 0.5 mg/kg and Phase Ia will be terminated. /Kg group if there are 2 or less cases of DLT.

(3) If none of the 3 patients in the 1.0 mg/kg group develop DLT, the MTD will be greater than 1.0 mg/kg and the Phase Ia portion will be terminated.

If 1 of 3 patients in the 1.0 mg/kg group develops DLT, enroll an additional 3 patients in the 1.0 mg/kg group; if 3 or more patients in the 1.0 mg/kg group develop DLT, the MTD will be 1.0 mg/kg and Phase Ia will be terminated. If DLT develops in 2 or fewer patients, the MTD will be 1.0 mg/kg. If fewer than 2 cases of DLT occur, the MTD will be greater than 1.0 mg/kg and Phase Ia will be terminated.

If the MTD is determined, investigational drug administration in the dose group corresponding to the MTD will be discontinued.

The safety evaluation for transfer to the next group (DLT observation period) can be determined based on information and test results up to 28 days after the start of the investigational drug administration, but the final safety evaluation period will be up to 24 weeks after the last dose in each case.

If more than 2 doses (including 1-week post-dose evaluation) cannot be administered during the DLT observation period (up to 28 days after the start of the investigational drug), except for cases in which dosing is postponed due to DLT, the case will be added to the same dosing group.

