**7-6. Expected number of cases to be enrolled**

**7-6-1. Phase Ia part**

0.1 mg/kg group 3 cases (maximum 6 cases)

0.5 mg/kg group 3 cases (maximum 6 cases)

1.0 mg/kg group 3 cases (max. 6 cases)

Total 9 cases (maximum 18 cases)

＜Rationale for setting the dose>

The dose was set up with reference to the usual Fibonacci's modification method in order to confirm safety up to 1.0 mg/kg, the dose for patients with ATL, while confirming that the dose limiting toxicity (DLT) does not exceed 2/6 (33.3%).

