**8-3. Definition of evaluation items**

**8-3-1. Definition of primary evaluation items**

1) Phase Ia

(1) Safety

The maximum tolerated dose (MTD) and dose-limiting toxicity (DLT) will be determined, and the type, frequency, and severity of adverse events will be observed. The Common Terminology Criteria for Adverse Events (CTCAE) v4.0 Japanese translation of the JCOG version^13)^ will be used for grading adverse events. Adverse events will be graded according to CTCAE v4.0.

The MTD is defined as the dose at which the number of subjects who developed DLT during the period up to 28 days after the start of treatment with the investigational drug was 3 or more. However, if the MTD is not reached at any dose, 1.0 mg/kg shall be the dose that was found to be well tolerated.

The observation period for DLT will be up to 28 days after the start of study drug administration. Among adverse events for which a causal relationship to the investigational drug cannot be ruled out, the following events will be considered DLTs.

Grade is determined according to CTCAE v4.0.

① Hematologic toxicity of Grade 4 or higher lasting for more than 7 days^*1^.

*1 "Febrile neutropenia" is defined as Grade 3 or higher regardless of duration, and "Neutropenia" is defined as treatment with G-CSF even if it is Grade 3 or lower. Lymphocytopenia" and "CD4 lymphocytopenia" are excluded.

② Non-hematologic toxicity of Grade 3 or higher

Symptoms judged to be "injection-related reactions" ("fever," "headache," "pain," "pruritus," "allergic reaction/hypersensitivity," etc.) are defined as Grade 4 or higher DLT. In addition, only AST (GOT), ALT (GPT), ALP, total bilirubin, creatinine, and potassium should be included in the clinical examination.

③ Others

i) Toxicity that caused the scheduled administration of the investigational drug to exceed 2 weeks beyond the specified scheduled administration date due to a Grade 3 in any of the symptoms judged to be "infusion-related reactions" in 2).

ii) Toxicities other than the above that prevented administration of the study drug more than twice during the DLT observation period due to the same event.

(2) Pharmacokinetics

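### The Phase Ia rules give no action for 2 DLTs in the first 3 patients, and at 1.0 mg/kg they contradict themselves and the MTD definition

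*Protocol*

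**What the plan says.** Protocol section 7-2 sets out the escalation rules dose by dose. At every dose, no DLT in the first three patients clears the dose and exactly one DLT triggers expansion.

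- **0.1 mg/kg.** Expansion: "If one of the three patients in the 0.1 mg/kg group develops DLT, three more patients will be enrolled in the 0.1 mg/kg group". Three or more DLTs makes 0.1 mg/kg the MTD and ends the study. Otherwise: "If DLT occurs in 2 or less cases, the patient will be shifted to the 0.5 mg/kg group". Neither of these last two rules says out of how many patients.
- **0.5 mg/kg.** The pattern is the same, but the stopping rule reads "If more than 3 patients in the 0.5 mg/kg group develop DLT, the MTD will be 0.5 mg/kg and Phase Ia will be terminated". The go rule is still two or fewer.
- **1.0 mg/kg.** Three or more DLTs makes 1.0 mg/kg the MTD. Two further sentences follow: "If DLT develops in 2 or fewer patients, the MTD will be 1.0 mg/kg" and "If fewer than 2 cases of DLT occur, the MTD will be greater than 1.0 mg/kg and Phase Ia will be terminated".

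Section 7-2 adds that once an MTD is determined, dosing stops in the group at that dose.

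Three other places bear on this. Section 8-3-1 defines the MTD as the dose at which the number of subjects with a DLT up to 28 days "after the start of treatment with the investigational drug was 3 or more", and names 1.0 mg/kg as the tolerated dose if no dose reaches that count. The design section of the protocol summary gives the same threshold. Section 7-1 sets the Phase Ib high dose at the highest tolerated dose ("one step below the MTD or 1.0 mg/kg if the MTD has not been reached"). Section 7-6-1 allows three to six patients per dose and takes a DLT level of 2/6 (33.3%) as the limit.

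**The concern.** The MTD is a primary endpoint of Phase Ia and fixes the high dose for Phase Ib. Three things in the rules that produce it do not work.

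1. **Two of three has no rule.** Expansion needs exactly one DLT. The stop and go counts come after the expansion step and have no denominator. After two of three, the Coordinating Committee would have to choose between stopping, expanding and escalating, and section 7-2 does not say which.
2. **At 1.0 mg/kg the text conflicts.** One DLT in six satisfies both closing sentences of 7-2(3), which place the MTD at 1.0 mg/kg and above it. Two in six gives an MTD of 1.0 mg/kg there but no MTD under 8-3-1.
3. **At 0.5 mg/kg the stop is off by one.** Exactly three DLTs is neither more than three nor two or fewer, so 7-2(2) gives no action, while 8-3-1 calls that dose the MTD.

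The second conflict changes the Phase Ib dose. With two DLTs in six at 1.0 mg/kg, following 7-2(3) stops dosing in that group and makes the Phase Ib high dose 0.5 mg/kg. Following 8-3-1 gives 1.0 mg/kg to 20 Phase Ib patients. The dosing rationale in section 7-1 itself expects a stronger immune response in solid tumors than in ATL.

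**Working it through.** **Outcomes set against the text**

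| Result at a dose | Section 7-2 | Section 8-3-1 |
|---|---|---|
| 0 of 3 | dose cleared | not MTD |
| 1 of 3 | add three | not MTD |
| 2 of 3 | not named at any dose | not MTD; no action given |
| 1 of 6 at 1.0 mg/kg | MTD is 1.0 and MTD is above 1.0 | not MTD |
| 2 of 6 at 1.0 mg/kg | MTD is 1.0 | not MTD |
| exactly 3 at 0.5 mg/kg | no action | MTD |

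The plan's own figures reproduce: 2/6 = 33.3%, 3 doses × 3 = 9 patients, 3 doses × 6 = 18 patients. If the two-or-fewer rule covered a first cohort, it would pass 2/3 = 66.7%, which is twice 33.3%.

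**How often these outcomes arise**

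The protocol gives no DLT rate for solid tumors, so the true rate p is assumed: 1/6 (the one in six seen at 1.0 mg/kg in the ATL Phase I study, section 1-3-2-1), 1/3 (the plan's limit) and 1/2 (a clearly too toxic dose). Write b(x) = C(3,x) pˣ (1−p)³⁻ˣ for x DLTs in three patients.

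| | p = 1/6 | p = 1/3 | p = 1/2 |
|---|---|---|---|
| b(0) | 0.579 | 0.296 | 0.125 |
| b(1) | 0.347 | 0.444 | 0.375 |
| b(2): two of the first three, no rule | 0.069 | 0.222 | 0.375 |
| b(1)·b(0): one of six, both closing sentences of 7-2(3) apply | 0.201 | 0.132 | 0.047 |
| b(1)²: two of six, 7-2(3) and 8-3-1 disagree | 0.121 | 0.198 | 0.141 |

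The last two rows are conditional on reaching 1.0 mg/kg. If two of three at 1.0 mg/kg were also read under the bare count, the disagreement would become b(1)² + b(2) = 0.190, 0.420, 0.516.

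**Chance of clearing 0.1 or 0.5 mg/kg, by handling of two of three**

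- Stops: b(0) + b(1)[b(0) + b(1)] = 0.900, 0.626, 0.313.
- Expands, and clears with two or fewer of six: the above + b(2)·b(0) = 0.940, 0.691, 0.359.
- Passed at once under the bare count: the first line + b(2) = 0.970, 0.848, 0.688.

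At p = 1/2, the chance of escalating past a too toxic dose is therefore 31%, 36% or 69%, depending on a choice that the protocol does not make.

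**The case against.** The best reply is that parts of 7-2 look like damaged translation. In 7-2(2) a sentence has lost its opening. The two closing sentences of 7-2(3) look like one sentence rendered twice, and similar doubling occurs in sections 1-3, 7-1 and 10-4. Read literally, the first of the two makes the expansion pointless, because three or more DLTs and two or fewer would both give an MTD of 1.0 mg/kg. The summary, 7-1, 7-6-1 and 8-3-1 all point one way: two of six at 1.0 mg/kg is tolerated and three at 0.5 mg/kg is the MTD. At 0.5 mg/kg the go rule still prevents escalation after three DLTs. On two of three, expansion is the only action that fits the MTD definition, the cap of six and the 2/6 limit, and a committee decides each transition in any case.

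Much of this is fair. A translation slip is a plausible origin for the 1.0 and 0.5 mg/kg wording, and the intended rule can be inferred. The 97%, 85% and 69% clearance figures, and the 19%, 42% and 52% disagreement figures, depend on a bare-count reading that was probably not meant. The 12%, 20% and 14% figures shrink once the chance of reaching 1.0 mg/kg is counted. If p were the same at all doses and two of three were expanded, they would be 0.121 × 0.940² = 11%, 0.198 × 0.691² = 9% and 0.141 × 0.359² = 2%.

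The reply does not remove the problem. The two-of-three omission is the same in all three paragraphs, so it is unlikely to be a slip, and correcting the other sentences would leave it in place. Inferring an action from four sections is not a stated rule. The current text, followed as written at 1.0 mg/kg, gives an MTD that the protocol's own definition rejects.

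**Conclusion.** The concern holds and should be fixed before the rules are applied. Section 7-2 has no action for two DLTs in the first three patients at any dose. At 1.0 mg/kg it contradicts itself for one DLT in six and contradicts 8-3-1 for two in six. At 0.5 mg/kg its stopping count disagrees with the MTD definition. These are defects of logic in the current text and do not depend on any assumed rate.

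The probabilities show only that the outcomes are not remote. With assumed true DLT rates of 1/6, 1/3 and 1/2, two of the first three occurs at a given dose with probability 7%, 22% and 37.5%. Once 1.0 mg/kg is reached, two in six by way of one and then one occurs with probability 12%, 20% and 14%. In that second case the choice of section decides between 0.5 and 1.0 mg/kg as the Phase Ib high dose.

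**What to change.** In section 7-2, at each of the three doses:

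- Trigger expansion to six when one or two of the first three patients have a DLT.
- State the go rule as two or fewer of six.
- State the MTD rule as three or more DLTs, including at 0.5 mg/kg.

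In 7-2(3), replace the two conflicting sentences with one: two or fewer DLTs in six means the MTD is not reached and 1.0 mg/kg is the tolerated dose.

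If the clinical team prefers to stop at two of three, section 7-2 should say so, and the MTD definition in 8-3-1 and in the summary should be extended to include it.

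The cost is protocol wording. Expanding after two of three adds up to three patients at that dose, within the existing maximum of 6 per dose and 18 in total.
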